The rationale for repeated measures of growth and development during the first 18 months of life is that frequent measurements until a later time point will more likely provide more accurate information on the dynamic process of infant growth and cognitive development. An advance attributed to the growing theoretical shift in the field of developmental psychology states that measuring the developmental course of cognitive function in infancy should be conducted within the realm of developmental systems theory[[190]](#endnote-190). Therefore, we will conduct more extensive longitudinal measurements and use measures of the developmental course of variables assessing whether nutritional supplementation affects cognitive outcome. The second methodological implication of the broader, developmental systems approach is that we will consider whether variables other than LCPUFA manipulations interact with the manipulations themselves. For example, it is possible that LCPUFA supplementation has larger effects in populations in which environmental quality (e.g., socioeconomic status or caregiver responsiveness) is poor, compared with populations in which environmental conditions are more optimal. A third implication is that small or transient effects at one age point may not be unimportant. The fact that there may be no differences in, for example, visual acuity at 6 months ignores the possibility that the acceleration of the visual acuity curve experienced by the supplemented group may have a longer-term effect. Thus, even a small early advantage in lower-order function may serve to affect higher-order functions at some later point. Further, in infancy the developmental process itself complicates the measurement of developmental functioning. For example, the Bayley may measure motor development well at 12 months, but be less valid for language development at this age as these skills are just emerging, or may be a predictor of intelligence at 24, but not at 6 months. There is also some evidence that among low-risk infants, scores within the first year of life are not predictive of later IQ, but those after 18-24 months provide more useful predictions; however, the instrument may be more predictive even within the first year of life among high-risk infants[[191]](#endnote-191). Similarly, growth faltering begins during the latter half of infancy and often continues through the second year of life. Although later prediction is not the main purpose of this study, the inclusion of these measurements will help our understanding of the underlying processes.

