Sample size calculations are based on the expected effect size, power to detect those differences and level of significance. The expected effect sizes for key outcomes presented in Table 3 were calculated by dividing the minimum meaningful difference (d) that we wish to detect by the standard deviation (S.D.) using data from either the literature or from our preliminary studies in Mexico and Guatemala. Most of the effect sizes are small to medium (0.2 to 0.5) and the minimum sample sizes required to detect them using a two-tailed test and confidence level of 0.05 are shown in Table 4 at different levels of power (80-95%)[[192]](#endnote-192). The smallest effect sizes of interest are 0.22 S.D. for birth weight and 0.25 S.D. for motor and mental development at 18 months of age. Using a two tailed test and a significance level of =0.05, a final sample of 338 infants per group at the end of the study will have 90% power to detect an effect size of 0.25 S.D. or greater for all the major outcomes. This sample size will have 80% power to detect meaningful differences in birth weight (0.22 S.D) as we expect at least 393 births/group after accounting for loss to follow-up (see section D 1.5). The power calculations are also presented for single outcomes as well as for repeated measures of growth and development assuming correlations of 0.2. Due to budgetary constraints, blood and breast-milk samples will be obtained for a 30% sub-sample of 120 mother-infant pairs per group, which will have 95% power to detect expected effect sizes of 0.5 S.D.

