**D.4.1. Overview of Statistical Approach**:

Generally, we will analyze outcomes from birth to 12 months of age among all children who reach that time point. In further analyses to be conducted in the subsample of children who are followed up until 18 months of age, missing interim endpoints will be imputed using multiple imputation procedures as described by Little and Rubin[[228]](#endnote-228). Effectiveness of randomization will be examined by comparing the two groups on key baseline characteristics. In the case of significant differences, group differences in outcomes will be examined with and without adjusting for these factors. Loss to follow-up is expected to be 20% to 18 months. We will assess selection bias by comparing baseline characteristics of subjects with and without the outcome measure of interest and control for any observed differences in the analyses.

All statistical analysis will be done using Statistical Analysis Software (SAS)[[229]](#endnote-229). A probability of p<0.05 will be considered statistically significant for all hypothesis testing. Assumptions of normality will be assessed using plots and tests of normality. Non-normal variables will be transformed or categorized as required. Descriptive data analysis will include examining the distributions of neurodevelopment, dietary intakes, anthropometric and PUFA status. Means, standard deviations, quartiles and median levels will be reported. Individual analytical hypotheses will be tested using the following general statistical techniques:

D.4.1.1. Outcomes measured at one time point: These are analyses which model outcomes collected at one point in time as a function of variables collected either cross-sectionally or longitudinally. For example, cognitive development at 18 months may be modeled as function of prenatal and postnatal growth, diet, and social confounding factors. These analyses can take several forms.

i. Analysis of Covariance will be used for comparison of means of two or more categories (e.g. supplement groups) adjusting for covariates, which may be either continuous or categorical.

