ii. General linear models based on least squares fit will be used when the dependent outcomes are continuous variables such as indicators of child growth and development and nutrient intakes. Independent variables can include continuous, categorical and dummy (0/1) variables. Two approaches, Ordinary Least Squares (OLS) regression and Two Stage Least Squares (2SLS) will be used, depending on the issues addressed.

iii. Logistic regression may be used if the response variable is dichotomous (e.g. stunting defined as ht/age Z score <= -2 ). Adjusted odds ratios will be calculated to estimate risk for the independent variable of interest namely supplement use while controlling for other confounding variables.

D.4.1.2. Outcomes measured on repeated occasions: Some of the data are obtained from repeated measurements on individuals over time (e.g. length measurements at birth, 1, 3, 6, 9, 12, and 18 months of age). Such longitudinal data are very useful for describing dynamic processes which would be poorly captured by a single outcome or "point prevalence" assessment. Independent variables can also be time varying (e.g. feeding practices by time period: 0-3, 3-6, 6-9, 9-12 and 12-18 months) or fixed (e.g. household SES). Examples of the variables we will be modeling longitudinally include:

- **Child outcomes:** birth size, growth, motor and mental development
- **Determinants of interest:** Supplement group
- **Controlling for confounding variables:** SES, maternal BMI, intelligence, home environment.

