**D.4.2. Analytical Plan:**

The principal outcome variables of interest will be birth outcomes (birth weight, length, maternal and newborn PUFA, neurodevelopment), breast milk PUFA levels, and child growth (weight, length, head circumference) and skinfold thickness) and development (cognitive and motor) at 18 months of age. In addition, weight and length gain from birth to 18 months of age, neurodevelopment at 1, 6 and 12 months, cognitive and motor development at 6 and 12 months and infant PUFA status at 1 and 3 months of age will also be examined. Preliminary descriptive analyses will be done to examine the distribution of the data and check for outliers, following which unadjusted comparisons of mean differences in length and weight and biochemical values will be made using Student's t test. The intervention groups will be compared on several baseline variables to ensure that randomization worked. Chi-square tests will be used to compare categorical variables and Student’s t test will be used to compare normally distributed continuous data. Following this, adjusted comparisons (using co-variance analysis)[[238]](#endnote-238) will be made if controlling for potential confounders is required using linear multiple regression for continuous variables and logistic regression for categorical variables[[239]](#endnote-239). In all cases, results will be presented before and after adjustment for confounding and testing of interactions.

Examples of some of the models for various hypotheses are presented below. For specific hypotheses 2a, using birth weight as the outcome of interest and general linear models regression analysis, we can test the following model:

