***2a. Birth weight = Constant + β1(Supplement)+ β2 (Other confounding)* *+ β3  (Supplement * other confounding)***

Similar models can be used to test specific hypothesis 3a and 3b using attained weight and length and cognitive and motor development at 18 months of age as the outcomes of interest. For example,

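### Supplement-by-covariate interactions may be declared significant at the full 5% on any outcome, so a spurious moderator could be reported even if DHA has no effect

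*Protocol*

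**What the plan says.** Section D.4.2 (Analytical Plan), after describing unadjusted and adjusted comparisons, states: "In all cases, results will be presented before and after adjustment for confounding and testing of interactions". The example models that follow (birth weight, 18-month length, 18-month mental development and the logistic model for stunting) each carry a product term, "Supplement * other confounding". Similar models are offered for the hypotheses on breast milk and blood fatty acids.

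Section D.4.1 sets one threshold: "A probability of p<0.05 will be considered statistically significant for all hypothesis testing". It makes no exception for interaction terms.

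Section D.1.2 gives the scientific motive: "we will consider whether variables other than LCPUFA manipulations interact with the manipulations themselves". It offers, as a possibility, larger effects where socioeconomic status or caregiver responsiveness is poor.

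Section D.4.1.2 lists four covariates, "SES, maternal BMI, intelligence, home environment", as examples of confounders for the longitudinal models. The principal outcomes are set out in D.4.2: "The principal outcome variables of interest will be birth outcomes (birth weight, length, maternal and newborn PUFA, neurodevelopment), breast milk PUFA levels", followed by growth, skinfold thickness and development at 18 months.

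The protocol gives no closed list of moderators, does not rank the interaction tests, does not call them exploratory and does not make them conditional on the overall comparison.

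**The concern.** More than a missing detail is at issue. The protocol takes a position: interactions are tested for every outcome, and one uncorrected threshold covers all tests. Under that rule each additional moderator or outcome is another 5% chance of a false positive when DHA has no effect in anyone. The product term is written with an open class of covariates, so the rule sets no upper limit on the number of tests.

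The sample size was set for main effects. A true interaction of the same size would usually be missed, so an isolated significant one is weak evidence.

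Section B.7 says the research may inform dietary recommendations. It does not mention subgroups, but a chance moderator could colour such advice. The investigators' summary of their earlier micronutrient trial, in the preliminary work, shows how this can happen. It first reports that a pregnancy weight-gain difference was not significant after adjustment. It then contrasts overweight with other women on weight change to one month post-partum, citing p<0.15 for the interaction.

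**Working it through.** **Inputs from the protocol.** Alpha is 0.05 (D.4.1) and two-sided (D.1.4: "Using a two tailed test and a significance level of" 0.05). Allocation is 1:1 (D.1.2). The final sample is given in D.1.4: "a final sample of 338 infants per group at the end of the study will have 90% power" for 0.25 SD. Four covariates are named as examples (D.4.1.2).

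The principal outcomes in D.4.2 come to 12 by my count:
- birth weight, birth length, maternal PUFA, newborn PUFA, birth neurodevelopment and breast milk PUFA;
- at 18 months, weight, length, head circumference, skinfold thickness, cognitive and motor development.

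**Inputs assumed.** These are the number of moderators and outcomes actually crossed, the correlations among outcomes and among moderators, and a moderator that splits the sample 50:50. The protocol gives none of these.

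**Step 1: reproduce the stated figure.** n per group = 2 × (1.960 + 1.282)² / 0.25² = 336.3, rounded up to 337, against 338 stated. With 338 per group, SE = √(2/338) = 0.0769 SD, 0.25/0.0769 = 3.25, and power = Φ(3.25 − 1.96) = 90.1%. The stated 90% is confirmed.

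**Step 2: chance of at least one false-positive interaction when DHA has no effect.** For k independent tests this is 1 − 0.95^k. For correlated tests, 200,000 sets of normal test statistics were drawn, taking the correlation between two tests as the outcome correlation times the moderator correlation, and counting any |z| > 1.96. The 12 × 1 lower figure comes from regression fits to 2,000 simulated null trials.

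| Outcomes × moderators | Tests | Independent | Correlated |
|---|---|---|---|
| Two 18-month Bayley scores × 1 | 2 | 9.8% | lower |
| 1 × 4 | 4 | 18.5% | 15% (moderators 0.5) |
| Two 18-month Bayley scores × 4 | 8 | 34% | 27% (both 0.5) |
| 12 × 1 | 12 | 46% | 31% (outcomes 0.5) |
| 12 × 4 | 48 | 91% | 72% (both 0.5); 49% (outcomes 0.8, moderators 0.5) |

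Fitting the interaction model to simulated null trials of 676, one moderator at a time, agrees: 91% and 73% for 12 × 4 at correlations 0 and 0.5. Intermediate assumptions for 12 × 4 give 89% (both 0.2), 86% (both 0.3) and 77% (outcomes 0.5, moderators 0.3). With independent tests, 48 × 0.05 = 2.4 false positives are expected. The 31% for one moderator is at outcome correlation 0.5; stronger correlation would lower it further.

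**Step 3: power for an interaction.** A 50:50 moderator gives 338/2 = 169 per cell. The difference between the two subgroup effects has SE = √(4/169) = 0.154 SD, twice the main-effect SE. For a 0.25 SD interaction, 0.25/0.154 = 1.625 and power = Φ(1.625 − 1.96) = 37%.

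**The case against.** Three stronger readings are tempting, and the documents do not support them.

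- **That the protocol prescribes 48 interaction tests.** It does not. The four covariates are listed as example confounders, not moderators. Adjusted comparisons are made where control is needed, and the equations are introduced as examples. The home-environment inventory is first collected at 6 months, so it makes little sense as a moderator of the six birth and breast-milk outcomes. Dropping those pairs leaves 42 tests (1 − 0.95^42 = 88% if independent), but the grid remains an illustration.
- **That a false claim of benefit in some subgroup is likely.** The calculation gives the chance of a significant interaction, which is not itself an efficacy claim. The protocol has no rule for drawing subgroup conclusions, and it requires results before interaction testing to be shown too. A figure above one half also needs several moderators and outcomes that are not too strongly correlated; one moderator gives 31–46% across 12 outcomes.
- **That effect modification is a formal aim.** None of the specific hypotheses concerns a moderator. The D.1.2 text is part of the rationale for repeated measurement and is tentatively worded.

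It can also be said that moderator lists and exploratory labels usually belong in a SAP, which may exist. That is fair as to the missing list. It does not answer the two general statements the protocol does make, which a SAP would have to override. Applying the threshold to interaction coefficients is an inference, since no interaction is a listed hypothesis, but it is the natural reading of a rule that covers all testing.

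**Conclusion.** The point holds in a limited form. As written, any supplement-by-covariate interaction on any outcome may be declared significant at 5%, and a spurious moderator could be reported when DHA does nothing. The size depends on how many tests are run, which the protocol leaves open: from at most about 10% in the narrowest case considered to about 49–91% for the full 12 × 4 grid. The larger figures are scenarios under assumed counts and correlations, not a consequence the protocol fixes. The 37% power figure assumes an evenly split moderator and the full final sample. Main-effect results are unaffected. The change should be made because it governs what the trial may conclude and costs very little.

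**What to change.** In D.4.1 and D.4.2, state that:
- the p<0.05 significance rule does not apply to supplement-by-covariate interactions;
- these interactions are exploratory and reported as estimates with confidence intervals;
- no subgroup efficacy conclusion is drawn from them.

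If the D.1.2 question about environmental quality is to be tested formally, one option is to pre-specify a single moderator fixed at baseline for the 18-month mental and psychomotor indices, with Holm adjustment over the two tests (the smaller p-value against 0.025, then the other against 0.05). Socioeconomic status would serve, since it is collected at recruitment. The home-environment inventory would not, since it is first measured at 6 months, after randomisation.

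The wording should not imply that uncorrected p<0.05 is acceptable across the many main-effect outcomes; that is a separate matter.

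The cost is a few sentences, with no new data and no extra participants. The downside is that subgroup findings could no longer be presented as confirmed.

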***2a. Birth weight = Constant + β1(Supplement)+ β2 (Other confounding)* *+ β3  (Supplement * other confounding)***

Similar models can be used to test specific hypothesis 3a and 3b using attained weight and length and cognitive and motor development at 18 months of age as the outcomes of interest. For example,

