Data on birth outcomes were available for 656 pregnancies, of which birth weight and length measurements were available for 97.4% (n=639) and 92.7% (n=608), respectively. One quarter of all recruited pregnancies was lost to follow-up. More than half (60%) of these losses occurred within the first 8 weeks of supplementation and were due to early pregnancy losses (intended and unintended abortions), dislike of supplement or refusal to participate. There were few (n=27) losses to follow-up that occurred after 20 weeks of supplementation. The reasons included migration out of the study area and lack of family support. Overall, compliance with the intervention and coverage for the range of measurements whether conducted at the study headquarters and at home was extremely high (95%).

Women in both groups were similar at recruitment for age, parity, economic status, height and hemoglobin (Hb), but not for marital status (4.6% and 2.2% of single mothers in the MM and FE groups) and body mass index (23.8 + 3.9 and 24.5 + 4.3 kg/m2 in the MM and FE groups). Loss to follow-up (25%) and compliance (95%) were similar for both groups. Mean birth weight (MM: 2.977 + 0.376 kg; FE: 2.959 + 0.429 kg) and length (MM: 48.62 + 1.93 cm; FE: 48.61 + 1.74 cm) were similar in both groups (MM: n=329; FE: n=327). Mean weight gain during pregnancy (recruitment to 37 weeks) was greater by about 600 g in the MM group (7.70 + 3.43 kg; n=287) compared to the FE group (7.08 + 3.68 kg; n=293), but these differences were not significant after adjusting for maternal weight at recruitment. There were also no differences in changes in MAC and skinfold thickness by intervention group. However, in the case of weight changes between recruitment and 1 mo post-partum, overweight women in the MM group gained 0.33 kg whereas those in the FE group lost 0.74 kg; non-overweight women had gained 3.14 and 3.05 kg, respectively (p<0.15 for the interaction term). *Although these findings suggest that MM supplements during pregnancy do not provide any added benefit compared to standard iron, examination of dietary data suggest that energy intakes were increased in the MM group.*

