**Table 3: Expected effect sizes for key study outcomes at birth and during the postnatal period**

| **Study Outcomes** | **Birth** | | | **Postnatal (3-18 mo)** | | |
| --- | --- | --- | --- | --- | --- | --- |
|  | ***S.D.*** | ***Minimum difference (d)*** | ***Effect Size*** | ***S.D*** | ***Minimum difference (d)*** | ***Effect Size*** |
| **GrowthError: Reference source not found** |  |  |  |  |  |  |
| Weight (kg) | 0.45 | 0.1 | **0.22** | 1.0 | 0.3 | **0.30** |
| Length (cm) | 1.6 | 0.5 | **0.31** | 3.0 | 1.0 | **0.33** |
| Head Circumference (cm) | 2.0 | 0.5 | **0.25** | 1.5 | 0.5 | **0.33** |
| Gestational Age (d) | 7.0 | 2.0 | **0.29** | - | - | **-** |
| **Development Error: Reference source not found***.****Error: Reference source not found*** |  |  |  |  |  |  |
| Brazelton Score | 1.0 | 0.8 | **0.80** | - | - | **-** |
| Fagan Test | - | - | **-** | 2.7 | 2.00 | **0.74** |
| Mental Development Index | - | - | **-** | 15 | 3.75 | **0.25** |
| Motor Development Index | - | - | **-** | 15 | 3.75 | **0.25** |
| **DHA statusError: Reference source not found*,Error: Reference source not found*** |  |  |  |  |  |  |
| Maternal blood***** | 1.0 | 0.50 | **0.5** | 1.0 | 0.50 | **0.50** |
| Infant blood***** | 1.0 | 0.50 | **0.5** | 1.0 | 0.50 | **0.50** |
| Breast milk (% TFA) | **-** | **-** | **-** | 0.08 | 0.04 | **0.50** |

**plasma phospholipid DHA levels expressed as % total fatty acids (TFA)*

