***3a. Length (18 mo) = Constant + β 1 (Supplement)+ β2 (Other confounding)* *+ β3  (Supplement * other confounding)***

***3b. Mental development ( 18 mo) = Constant + β1 (Supplement)+ β 2 (Other confounding)* *+***

***β3  (Supplement * other confounding)***

Similar models can be specified to test the hypotheses stated under specific aims 1 & 4, for example that breast milk PUFA levels and infant PUFA status at 1 month of age will be higher in the intervention group compared to ‘control’ group. Mean values of breast milk and blood levels of DHA will be used as the dependent variables. Since some outcomes will also be defined as dichotomous outcomes, some of the hypotheses will also be tested using logistic regression. For example, if the dependent variable for specific hypothesis 3a is prevalence of stunting at 18 months of age that is defined using cut-offs for height/age Z score (HAZ), the model will be as follows:

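### The example models for hypotheses 2a, 3a, 3b and stunting include a supplement-by-covariate term, so their β1 is not the average DHA effect the trial is powered for, and no result is named as decisive

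*Protocol*

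**What the plan says.** The hypotheses in D.1.1 are comparisons of supplemented and placebo groups as wholes. The sample size in D.1.4 is built the same way, on a difference between two group means.

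D.4.2 then gives example models. For hypothesis 2a it says that, "using birth weight as the outcome of interest and general linear models regression analysis, we can test the following model". That model starts "Birth weight = Constant + β1(Supplement)+ β2 (Other confounding" and adds a third coefficient, β3, on "Supplement * other confounding". Models 3a (length at 18 months) and 3b (mental development at 18 months) have the same three terms, as does the model for stunting at 18 months. D.4.2 also says that similar models can be set up for aims 1 and 4.

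Nothing in the section says that covariates are centred, which coefficient or contrast tests the hypothesis, or when the product term is dropped. The covariates are not listed beside the equations. D.4.1.2 gives SES, maternal BMI, maternal intelligence and home environment as the confounders to control for.

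Other analyses are planned too. D.4.2 starts with unadjusted t tests for length, weight and biochemical values, moves to covariance analysis if adjustment is needed, and promises results both before and after adjustment and interaction testing. D.4.1.1 lists analysis of covariance for comparing supplement groups. Section E.10 makes child development the primary outcome.

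**The concern.** In a model with a treatment-by-covariate product, the coefficient on treatment alone is the treatment effect at covariate value zero. For a covariate such as maternal BMI, zero is impossible, so β1 describes no real mother. It equals the average effect only if the effect does not vary with the covariate or if the covariate is centred at its mean. Even when the effect is constant, so that β1 is unbiased for it, the estimate is an extrapolation far from the data and its standard error grows.

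The equations written for the hypotheses therefore do not isolate the quantity that the hypotheses state and the sample size was chosen to detect. Because no result is named as decisive, an analyst could report β1 from the written model, a main-effects estimate or an unadjusted difference. These can have very different precision. The gap matters most for development: it is the primary outcome, the t-test sentence does not name it, and the equation shown for it (3b) includes the product term.

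**Working it through.** **Inputs**

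- Significance level: "A probability of p<0.05 will be considered statistically significant for all hypothesis testing" (D.4.1).
- Two-sided test (D.1.4): "Using a two tailed test and a significance level of" 0.05.
- Sample size and power (D.1.4): "a final sample of 338 infants per group at the end of the study will have 90% power" for 0.25 SD.
- Mental development effect (Table 3): 3.75 / 15 = 0.25 SD.
- Birth weight effect (Table 3): 0.1 / 0.45 = 0.22 SD, with 393 births per group expected (D.1.4).
- Maternal BMI, from the team's earlier micronutrient trial described in section C: "body mass index (23.8 + 3.9 and 24.5 + 4.3 kg/m2" in its two arms. This is an assumption for the present population.

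**Step 1: reproduce the plan's figure.** For a two-group comparison with no product term, n per group = 2(1.960 + 1.282)² / 0.25² = 336.2, rounded up to 337. At 338 per group the standard error is √(2/338) = 0.0769 SD and 0.25 / 0.0769 = 3.25, which gives 90.1% power. The stated 338 and 90% are confirmed. For birth weight, 0.22 SD at 393 per group gives 87%, so the stated 80% is conservative.

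**Step 2: standard error of β1 with the product term.** With 1:1 randomisation, residual variance σ² and n per group,

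Var(β1) = (2σ²/n) × [1 + (mean/SD)²],

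where mean and SD are those of the covariate as coded. For a 0/1 covariate with proportion p coded 1, the bracket equals 1/(1 − p). A centred covariate has mean zero, so the bracket equals 1.

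**Step 3: power of the β1 test.** This assumes a constant treatment effect (true β3 = 0) and a covariate that explains no outcome variance.

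| Covariate coding | Variance factor | SE multiplier | Power, 0.25 SD, 338/group | Power, 0.22 SD, 393/group |
| --- | --- | --- | --- | --- |
| Centred, or no product term | 1.00 | 1.00 | 90% | 87% |
| 0/1, 25% coded 1 | 1.33 | 1.15 | 80% | 76% |
| 0/1, 50% coded 1 | 2.00 | 1.41 | 63% | 59% |
| 0/1, 75% coded 1 | 4.00 | 2.00 | 37% | 34% |
| BMI uncentred, 24.5 (SD 4.3) | 33.5 | 5.8 | 8.7% | 8.3% |
| BMI uncentred, 23.8 (SD 3.9) | 38.2 | 6.2 | 8.2% | 7.9% |

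Worked example, last row: 1 + (23.8/3.9)² = 38.2 and √38.2 = 6.18. The standard error is 0.0769 × 6.18 = 0.475 SD and 0.25 / 0.475 = 0.53. Two-sided power is Φ(0.53 − 1.96) + Φ(−0.53 − 1.96) ≈ 0.08.

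**Step 4: check by simulation** (4,000 trials per setting). With BMI 23.8 (SD 3.9), 338 per group and 0.25 SD, rejection rates were 89% unadjusted, 89% for covariance analysis, 8.1% for β1 with the raw product term and 89% for β1 with the centred product term. With a 50% binary covariate the four rates were 90%, 90%, 62% and 90%.

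With several uncentred covariates entered together, the loss is at least as large as for the worst of them alone. The formula is for the linear models and does not give a figure for the logistic stunting model.

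**The case against.** The strongest reply is that D.4.2 presents these equations as examples of what can be fitted, uses a placeholder for the covariates and never says that β1 is the test statistic. The average effect can be recovered from the same fit by evaluating it at the covariate mean, with no loss of power. Centring and choice of contrast are ordinary matters for an analysis plan that is not shown here. The product term is also deliberate: D.1.2 says the team wants to know whether other variables modify the supplement effect. Finally, the unadjusted comparisons, covariance analysis and before-and-after reporting keep the planned power.

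Most of this stands. A reader might infer that the trial as planned loses almost all its power, or that a real DHA effect would be reported as null. The documents do not support either reading. Both require that β1 from an uncentred model be the deciding test, which no sentence says, and analyses without the product term are to be reported in all cases. The 8–9% figure also belongs to one kind of covariate, with inputs from another trial.

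The reply does not remove the mismatch on the page. The protocol itself chose to write a model for these hypotheses, and each time it included a term that changes what β1 means. The stunting model, though introduced as an example, is worded more firmly than the others. For development, the main-effect result rests only on the general before-and-after sentence and the general mention of covariance analysis. Nowhere is one result said to decide a hypothesis.

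**Conclusion.** The point holds as a defect in how the hypothesis models are written. In models 2a, 3a, 3b and the stunting model, β1 is the DHA effect at covariate value zero, whereas D.1.1 states, and D.1.4 powers, an average group difference. The protocol plans analyses that do estimate that difference but does not say that they decide.

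The size is conditional. If β1 were tested with uncentred covariates, power for 0.25 SD at 338 per group would be about 8–9% for a covariate like BMI and 80% to 37% for the 0/1 covariates examined, against 90% planned. If covariates are centred or the product term is omitted, the loss is nil. These figures assume a constant effect, a covariate unrelated to outcome and, for BMI, the earlier trial's distribution.

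**What to change.** In D.4.2, write the test of each hypothesis as the main-effects model, outcome = constant + β1(Supplement) + β2(baseline covariates), on the logit scale for stunting. State that β1 from this model is the trial result for that hypothesis, whatever the interaction tests show, and say explicitly that this covers mental and motor development. Move the supplement-by-covariate terms, with covariates centred, to separate secondary analyses of effect modification, which keeps the question raised in D.1.2. The cost is wording only: sample size, data collection and schedule are unchanged.
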